The *zhenjia* theory is first mentioned in the *Inner Canon of the Yellow Emperor* (*Huang di Nei jing*). *Zhenjia* refers to a complex of phlegm, stasis, heat, and damp that mainly forms and exists in collaterals. In CKD, *zhenjia* forms in the collaterals of the kidney and exacerbates kidney injury. TCHM can help dissolve *zhenjia*. Our previous studies have shown that a formula based on the *zhenjia* theory can decrease urinary albumin and serum creatinine (Scr) levels and suppress interstitial expansion and glomerulosclerosis in rats with DKD. These therapeutic effects might be related, at least partially, to the inhibition of inflammatory response and extracellular matrix accumulation mediated by the TNF-α/NF-κBp65 signaling pathway [16]. According to the *zhenjia* theory, the composition of *zhenjia* is different in different stages of DKD. Thus, *zhenjia* is mainly composed of heat, stasis, and turbidity toxin in the early, middle-, and advanced-DKD stages, respectively. Therefore, it is necessary to dissipate the heat, remove the blood stasis, and dislodge the turbid toxin. Accordingly, we prescribe different formulas to patients with DKD of different stages. The *Tourexiaozhen* formula is prescribed to patients with early stage DKD to dissipate heat; the *Huoxuexiaozhen* formula is utilized for middle-stage DKD to remove blood stasis; while the *Xiezhuoxiaozhen* formula is employed for advanced-stage DKD to dislodge the turbid toxin. The proposed study will be designed as a randomized controlled trial that evaluates DKD treatment according to the disease stages. In order to recapitulate the real-world practice of TCM, it will be possible to adjust each formula individually according to the patient’s signs and symptoms.

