### Randomization and blinding

The random sequence will be generated by the Center for Evidence-Based Medicine of Beijing University of Chinese Medicine using Statistical Analysis System (SAS version 9.2), and randomization will be stratified according to study center and DKD stage. Eligible patients with DKD of each stage will be randomized to the experimental group or the control group at a 1:1 ratio. The group numbers will be provided in envelopes made from carbonless paper. At each center, the envelopes will be kept by a study administrator who will not directly participate in the recruitment or follow-up of any participant, and the group numbers will be subsequently disclosed. The administrator will open one envelope and provide the participant with their group number on the day of inclusion.

Different people will serve as investigators, therapists, and assessors. Assessors of primary and secondary endpoints and data analysts will be blinded to the treatment allocation throughout the course of the study, while patients, investigators, and therapists administering the treatment will not be blinded.

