#### Experimental group

In addition to the above-mentioned basic treatment, participants in the experimental group will receive an oral traditional Chinese formula based on the *Zhenjia* theory, which is different for different stages of DKD. The *Tourexiaozhen* formula for participants with early stage DKD will consist of *Radix scutellariae* (*Huang Qin*), *Fructus forsythiae* (*Lian Qiao*), *Fructus arctii* (*Niu Bang Zi*), and *Radix scrophulariae* (*Xuan Shen*); the *Huoxuexiaozhen* formula for those with middle-stage DKD will include *Fructus arctii* (*Niu Bang Zi*), *Abelmoschus corolla* (*Huang Shu Kui Hua*), *Sargassum* (*Hai Zao*), *Hirudo* (*Shui Zhi*), and *Radix astragali* (*Huang Qi*); and the *Xiezhuoxiaozhen* formula for end-stage DKD will include *Radix astragali* (*Huang Qi*), *Cortex eucommiae* (*Du Zhong*), *Eupolyphaga seu steleophaga* (*Tu Bie Chong*), *Sargassum* (*Hai Zao*), *Radix et rhizoma rhe* (*Da Huang*), and *Rhizoma smilacis glabrae* (*Tu Fu Ling*). The ingredients in each formula can be adjusted individually at every visit according to patient’s signs and symptoms, and the dose of each ingredient in the prescription will be decided by the physician. The standard adjustments will be as follows: for patients with dry mouth or thirst, *Radix puerariae* (*Ge Gen*) will be added to the formula; for patients with bitter taste, *Radix bupleuri* (*Chai Hu*), *Radix scutellariae* (*Huang Qin*), and *Fructus aurantii immaturus* (*Zhi Shi*) will be added to the formula; for patients with low back pain, *Radix cyathulae* (*Chuan Niu Xi*), *Dipsaci radix* (*Xu Duan*), and *Rhizoma cibotii* (*Gou Ji*) will be added to the formula; for patients with edema, *Polyporus* (*Zhu Ling*), *Poria* (*Fu Ling*), *Rhizoma alismatis* (*Ze Xie*), *Pericarpium arecae* (*Da Fu Pi*), and *Exocarpium benincasae* (*Dong Gua Pi*) will be added to the formula; for patients with abdominal distension, *Radix aucklandiae* (*Mu Xiang*), *Fructus amomi* (*Sha Ren*), *Citrus medica* (*Xiang Yuan*), and *Fructus citri sarcodactylis* (*Fo Shou*) will be added to the formula; and for patients with itching skin, *Fructus kochiae* (*Di Fu Zi*) will be added to the formula. All formulae will be prescribed by a physician licensed in Chinese medicine and with at least 8 years of clinical experience. The formulae will be prepared in the form of granules by Beijing Tcmages Pharmaceutical Co., Ltd. (Beijing, China), a company that has passed the Chinese Good Manufacturing Practice for Pharmaceutical Products certification. A single-day supply will be provided in two doses (pouches) to be taken orally one at a time (twice a day).

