#### Safety outcomes

Complete blood count (CBC), AST, ALT, alkaline phosphatase (ALP), glutamyl transpeptidase (GGT), and total bilirubin (TBIL) tests and electrocardiography will be performed at baseline and at every study visit. The proportion of patients demonstrating adverse drug reactions (ADRs) in the experimental group will be compared with that in the control group. ADRs will be defined as undesirable, unexpected symptoms, signs, or diseases that occur during the clinical trial and can be caused by the treatment.

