### Statistical analysis

Statistical analysis will be conducted at the Center for Evidence-Based Medicine of Beijing University of Chinese Medicine using Statistic Package for Social Science (SPSS, version 22.0, Beijing University of Chinese Medicine). Intention-to-treat and per protocol sets will be used to analyze the efficacy of TCHM. A safety analysis set will be used to evaluate the safety of the trial. Missing outcome variables will be estimated using the principle of the last observation carried forward, with the data from the last study follow-up used as the final results.

The independent-samples *t* test or Mann-Whitney test will be used for comparison of the trial primary outcomes between the two groups, including UAER in the early stage subgroup, 24-h UP in the middle-stage subgroup, and eGFR in the advanced-stage subgroup, which are all continuous variables with four measurements. Moreover, repeated measures analysis of variance will be attempted to further test the time effect and treatment cross-effect. With regard to the secondary outcomes, the independent-samples *t* test or Mann-Whitney test will be used to analyze continuous variables, and the chi-squared test will be used to analyze classified variables. With regard to safety outcomes, the incidence of AEs will be determined and a comparison between the two groups will be attempted. A stratified analysis of data according to DKD stage or center will be attempted in order to decrease bias. A *P* value < 0.05 will be considered to indicate a statistically significant difference.

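### The adverse-event comparison, and several secondary outcomes, are not tied to DKD stage although stage determines the formula; analysis by stage is only to be attempted, as an alternative to center

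*Protocol article*

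**What the plan says.** - **Treatment.** Under Experimental group, "participants in the experimental group will receive an oral traditional Chinese formula based on the *Zhenjia* theory, which is different for different stages of DKD". There are three base formulas, one per stage.
- **Aim and randomization.** The Background describes a trial that "evaluates DKD treatment according to the disease stages". Under Randomization and blinding, "randomization will be stratified according to study center and DKD stage", at 1:1 within each stage.
- **Primary outcomes.** Statistical analysis ties each one to a stage: "including UAER in the early stage subgroup, 24-h UP in the middle-stage subgroup, and eGFR in the advanced-stage subgroup".
- **Secondary outcomes.** The same section says: "With regard to the secondary outcomes, the independent-samples *t* test or Mann-Whitney test will be used to analyze continuous variables". No stage is named. The Secondary outcomes section lists the physicochemical measures separately by stage, but lists the TCM syndrome score, SF-36, CRP, IL-6 and TNF-α without one.
- **Safety.** Under Safety outcomes: "The proportion of patients demonstrating adverse drug reactions (ADRs) in the experimental group will be compared with that in the control group". Under Statistical analysis: "the incidence of AEs will be determined and a comparison between the two groups will be attempted". Neither sentence names a stage.
- **Provision for stage.** "A stratified analysis of data according to DKD stage or center will be attempted in order to decrease bias".

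**The concern.** The trial amounts to three parallel randomized comparisons, one per stage, each with its own base formula, primary outcome and sample size. For safety, and for the secondary outcomes listed without a stage, the text no longer follows that structure. By-stage analysis is optional, is offered as an alternative to center, and is justified as reducing bias. Bias is not the main reason to want it, because 1:1 allocation within stage already balances stage between arms, leaving aside differential dropout. The reasons are attribution and precision.

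Two things are at stake. A reaction caused by one formula could be averaged with patients who never received that formula. And because the text leaves the choice open, by-stage or pooled reporting could be chosen after the results are seen.

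**Working it through.** **1. The plan's own sizes are built by stage.** Inputs are the pilot means and SDs in the Sample size section, z values 1.64 and 1.28, and 20% dropout. Per arm, n = (1.64 + 1.28)² × (s₁² + s₂²) / (difference)², with (1.64 + 1.28)² = 8.5264.

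- Early: 8.5264 × (51² + 27²) / 26² = 8.5264 × 3330 / 676 = 42.0; 42 / 0.8 = 52.5, so 53.
- Middle: 8.5264 × (1.09² + 0.95²) / 0.75² = 8.5264 × 2.0906 / 0.5625 = 31.7, so 32; 32 / 0.8 = 40.
- Advanced: 8.5264 × (9.1² + 10.2²) / 7.1² = 8.5264 × 186.85 / 50.41 = 31.6, so 32; 32 / 0.8 = 40.
- Total: 2 × (53 + 40 + 40) = 266.

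All the stated figures reproduce. Each rests on a within-stage comparison; none rests on a pooled one.

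**2. Dilution in a pooled safety comparison.** Each arm has 133 patients. The early formula supplies 53/133 = 39.8% of the experimental arm, and the middle and advanced formulas 40/133 = 30.1% each. An excess risk confined to one formula is multiplied by that share. The documents give no reaction rates, so the rates below are assumptions. The pooled experimental rate is (n × p₁ + (133 − n) × p₀) / 133, where n is the number per arm in the affected stage, p₁ the raised rate and p₀ the rate elsewhere. For 5% everywhere except 20% under one middle- or advanced-stage formula, it is (40 × 0.20 + 93 × 0.05) / 133 = 9.5%, so a 15-point excess becomes 4.5 points. For the early formula it is (53 × 0.20 + 80 × 0.05) / 133 = 11.0%, an excess of 6.0 points.

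Power of a two-sided 5% two-proportion test (normal approximation, enrolled numbers):

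| Assumed rates | Stage affected | Within stage | Pooled |
|---|---|---|---|
| 5% vs 20% | middle or advanced | 53% | 29% |
| 5% vs 20% | early | 65% | 43.5% |
| 2% vs 20% | middle or advanced | 74% | 55% |
| 10% vs 30% | middle or advanced | 61% | 31% |

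**3. The opposite case: a shared herb.** Fructus arctii is in the early and middle formulas; Radix astragali and Sargassum are in the middle and advanced ones. At the same 5% and 20%:

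- Harm in early and middle: pooled rate (93 × 0.20 + 40 × 0.05) / 133 = 15.5%; pooled power 81%, against 65% or 53% within one stage.
- Harm in middle and advanced: pooled rate (80 × 0.20 + 53 × 0.05) / 133 = 14.0%; pooled power 71%, against 53% within one stage.

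**4. Precision of a pooled test on a continuous outcome.** If stage explains a share R² of the within-arm variance, a two-group test that ignores stage overstates the standard error by f = 1/√(1 − R²). Its actual two-sided level is 2(1 − Φ(1.96f)). For a comparison with 80% power when stratified, its power is Φ(2.80 − 1.96f). R² is assumed.

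| R² | f | Actual level | Power |
|---|---|---|---|
| 0.1 | 1.054 | 3.9% | 77% |
| 0.3 | 1.195 | 1.9% | 68% |
| 0.5 | 1.414 | 0.6% | 51% |

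The error is conservative: power is lost, and no false positives are created.

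**The case against.** Three stronger readings are tempting, and the document supports none of them.

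**That all secondary outcomes are pooled.** The text does not say so. It names tests and no population. The physicochemical outcomes are listed by stage, and the article uses the same two-group language for comparisons that are plainly within stage, such as the primary ones. Pooling is therefore an inference, most plausible for the TCM score, SF-36 and the inflammation markers. The upper end of the precision range would suit serum creatinine best, since stage is defined partly by eGFR, but creatinine is one of the outcomes listed by stage.

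**That a pooled result would be invalid or meaningless.** Allocation is 1:1 within stage, so a pooled contrast is an unconfounded estimate of the stage-adapted strategy, and the Discussion does speak of the effect of xiaozhen therapy as a whole. Physicians may also adjust ingredients at every visit, so even a within-stage result does not isolate one fixed formula. The limits are attribution, dilution and precision.

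**That pooling always hides harm.** It does so when the harm is confined to one formula. With a herb shared by two formulas, the all-stage comparison has more power than any single stage.

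It can also be said that an article leaves table populations to the full protocol or analysis plan. That would answer a complaint about missing detail. Here the article does state a rule for stage, and the rule is optional, interchangeable with center, and given the wrong rationale. Finally, analysing everything in three stages adds comparisons. That stands, and it shapes the fix.

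**Conclusion.** The point holds in limited form. The AE and ADR comparison reads as all-stage, several secondary outcomes are left without a stage, and the only safeguard is an attempt at stratifying by stage or by center. An unstratified all-stage test would be valid for the strategy but not attributable to a formula.

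An excess risk confined to one formula would shrink to 30% or 40% of its size; these shares follow from the planned numbers. The power losses (53% to 29%, or 65% to 43.5%, at 5% vs 20%) rest on assumed reaction rates and on harm confined to one formula. The 5–41% overstatement of the standard error rests on an assumed R² of 0.1 to 0.5 and applies only where outcomes are in fact pooled without stratification. The planned primary comparisons are untouched. This should be corrected, because the strata are already randomized and the change is small.

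**What to change.** In Statistical analysis, replace the sentence that begins the provision for stage with a fixed rule, and align Safety outcomes with it:

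- Report AE and ADR rates and each secondary outcome by stage, as between-arm estimates with confidence intervals, and state that these are descriptive.
- Stratify any all-stage comparison by stage: stage as a factor in the linear model, the van Elteren test in place of Mann-Whitney, and a Mantel-Haenszel risk difference for AEs and ADRs. Label the result as the average effect of the stage-adapted strategy.
- Drop the bias rationale and the choice between stage and center.

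The all-stage summary keeps the full sample and, with it, the power to detect harm from shared herbs. The cost is a few sentences and extra table columns, with no new data. By-stage estimates will be imprecise at 40–53 per arm and add comparisons, so they should not carry confirmatory claims.

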## Discussion

DKD is a worldwide health problem. It has been estimated that approximately 25–40% of patients with DM will develop DKD [20]. Compared to non-diabetic CKD, DKD progresses more rapidly to ESRD [21, 22]. Moreover, owing to other concomitant complications of DM, such as diabetic retinopathy and diabetic foot, patients with DKD are often in poor health and have low quality of life. TCHM has been long used to treat complications of DM, including DKD, and has a great ability to improve patients’ quality of life. As we know, TCM is an individual treatment based on the theory of syndrome differentiation. A prescription usually consists of several well-chosen herbs is one of the inherent characteristics of TCM, while sometimes it needs adjustments owing to its principle of individual treatment. Chinese herbal medicine has been proved as an effective way to treat DKD by many researchers. However, most of the reported formula was unified prescription or a single herb under ideal circumstances. Here, we try to explore an effective research method to show the effect of *xiaozhen* therapy in DKD patients and reflect the characteristic of TCM as our real daily clinical practice. So, our study is designed as a randomized controlled trial in which all participants will be randomly assigned either to the control group or the experimental group, with very similar controlled conditions in the two groups. Simultaneously, it is a pragmatic trial in which the ingredients of the formula can be adjusted by physicians according to patient’s symptoms and signs. This is more in accordance with the above characteristic of TCM. Recently, a prospective research study from Taiwan has shown that patients with CKD who used prescription Chinese medicine had a significantly (60%) reduced ESRD risk [23]. A similar study for DKD is lacking. Our study has the potential to contribute to the development of an effective DKD treatment.

Some limitations of our study should be acknowledged. First, there may be differences between the six centers included in the trial in terms of experience in using TCHM for DKD. Therefore, a strict training and supervision system will be implemented to ensure that the trial is as homogeneous and consistent as possible. Second, because participants will not be blinded to their allocation, assignment to the unwanted group may result in poor compliance. We will describe the trial to the participants before they enter the study and perform telephone follow-up to avoid this potential problem. Last, the sample size of this study was based on our preliminary study while taking herbal therapy including the adjustments as an interfering group, the samples of our study may be different if each adjustment be considered separately. As a trial in TCM research, it needs more improvements in the future.

## Trial status

We are currently recruiting participants.

## Abbreviations

24-h UP: 24-h urinary protein
ACEI: Angiotensin converting enzyme inhibitor
ACR: Albumin-to-creatinine ratio
ADR: Adverse drug reaction
AE: Adverse event
ALP: Alkaline phosphatase
ALT: Alanine aminotransferase
ARB: Angiotensin receptor blocker
AST: Aspartate transaminase
BUN: Blood urea nitrogen
CBC: Complete blood count
CKD: Chronic kidney disease
CRF: Case report form
CRP: C-reactive protein
DKD: Diabetic kidney disease
DM: Diabetes mellitus
eGFR: Estimated glomerular filtration rate
ESRD: End-stage renal disease
GGT: Glutamyl transpeptidase
HbA1c: Glycated hemoglobin
IL-6: Interleukin-6
KDIGO: Kidney Disease Improving Global Outcomes
NKF-KDOQI: National Kidney Foundation Kidney Disease Outcomes Quality Initiative
RAAS: Renin-angiotensin-aldosterone system
SAE: Severe adverse event
SAS: Statistical Analysis System
SBP: Systolic blood pressure
Scr: Serum creatinine
SF-36: Short Form 36-item Health Survey
SPSS: Statistic Package for Social Science
TBIL: Total bilirubin
TCHM: Traditional Chinese herbal medicine
TCM: Traditional Chinese medicine
TNF-α: Tumor necrosis factor α
UAER: Urinary microalbumin excretion rate
